
### Missing data

According to Little and Rubin [28], the missing-data mechanism will be performed through the multiple imputation method, to replace missing values and to calculate accurate estimates of standard errors. The procedures all rest on the assumption that data are missing at random (MAR). We will include all non-missing values or outcomes at all time points and baseline demographics in the models that generated imputed estimates (that is, the likelihood of missing a follow-up visit can be predicted by available baseline or past observed data [29]). In addition, the multiple imputation method combines the likelihood-based analysis from each completed dataset is approximately equivalent to the analysis based on the observed-data likelihood, whereas the imputation uncertainty is reflected by the variation across the multiple completed datasets [30]. According to the definition of Fisher *et al.*[31], the intent-to-treat analysis will be include all randomized patients in the groups to which they were randomly assigned, regardless of their adherence with the entry criteria, regardless of the treatment they actually received, and regardless of subsequent withdrawal from treatment or deviation from the protocol [32]. The variable follow-up time for individual subjects, both the number of relapse events and duration of relapses during the follow-up will be calculated as the number (or duration (weeks)) of events per person per year of follow-up.

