### Sample size calculation

The sample size and power were calculated using EpiInfo™ version 6.04 (Centers for Disease Control and Prevention, Atlanta, GA, USA). Assuming readmissions will be 50% in the control group and 30% in the intervention group, with a confidence of 95% and a power of 80%, it would be required to include at least 166 patients. The estimated sample size of 200 patients with a BD-I diagnosis is needed to cover losses during the follow-up and to increase sensitivity towards secondary objectives.

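### The imputation model as listed does not name randomised arm; followed literally, it would pull the between-arm difference toward zero, so arm should be written in

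*Protocol article*

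**What the plan says.** The Missing data section of the protocol article commits to multiple imputation under a missing-at-random assumption and describes the model: "We will include all non-missing values or outcomes at all time points and baseline demographics in the models that generated imputed estimates". It explains the assumption by saying that "the likelihood of missing a follow-up visit can be predicted by available baseline or past observed data". The same section says that "the intent-to-treat analysis will be include all randomized patients in the groups to which they were randomly assigned". The purpose of the completed data is therefore a comparison between the randomised arms, as the Biostatistical considerations section confirms.

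The article gives no expected loss rate. Its sample size section sets a minimum of 166 and recruits 200, the excess being "needed to cover losses during the follow-up and to increase sensitivity towards secondary objectives".

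**The concern.** The section does not merely leave the imputation model to a later document. It gives a list of contents, and the variable that the analysis compares is not on it. Imputation should condition on every variable in the analysis model. If arm is left out, a control patient and an intervention patient with the same observed outcomes and demographics receive imputed values from the same distribution. The part of the treatment effect that those predictors do not carry is then set to zero among the imputed values.

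Arm may also predict who is missing. Intervention patients have weekly calls and appointments, while control patients are scheduled to meet the pharmacist every three months, with some calls to encourage attendance. Unequal contact makes unequal retention plausible, and missing at random is easier to defend when arm is conditioned on.

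At stake is an intention-to-treat estimate that could understate the effect, and could do worse than an analysis of the observed patients alone.

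**Working it through.** **Inputs.** From the sample size section: "Assuming readmissions will be 50% in the control group and 30% in the intervention group", and "with a confidence of 95% and a power of 80%, it would be required to include at least 166 patients"; 200 are recruited. From Biostatistical considerations: two-tailed tests at 0.05. From Randomization: equal allocation, so 100 per arm. The loss rate m is an assumption. (200 − 166)/200 = 17% is the largest loss the recruitment margin can absorb.

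**The plan's own figure.** With p1 = 0.5, p2 = 0.3, mean p = 0.4 and difference d = 0.2, the Fleiss formula per arm is n = [z_α √(2p(1−p)) + z_β √(p1(1−p1) + p2(1−p2))]² / d².
- Two-sided 0.05: (1.960 × 0.6928 + 0.8416 × 0.6782)² / 0.04 = 93 per arm, 186 in total (206 with continuity correction).
- One-sided 0.05: 74 per arm, 148 in total; with continuity correction 83 per arm, 166 in total.

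So 166 is reproduced only as a one-sided, continuity-corrected figure. That is a separate matter, but it means the 80% is not a firm benchmark for the two-tailed tests. All power figures below are two-sided and uncorrected: power = Φ{[d√n − 1.960 √(2p(1−p))] / √(p1(1−p1) + p2(1−p2))}. With complete data at n = 100 this is 82.8%.

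**Worst case without arm.** Take equal loss m in both arms and predictors that carry no information about outcome. Every imputed value then has mean 0.4, whichever the arm:
- control: (1 − m) × 0.5 + m × 0.4
- intervention: (1 − m) × 0.3 + m × 0.4
- difference: 0.2 × (1 − m)

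At m = 0.17: 0.415 + 0.068 = 0.483 and 0.249 + 0.068 = 0.317, a difference of 0.166.

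| Assumed loss | Difference, arm omitted (points) | Power at 100 per arm, before imputation variance | Power, observed patients only (n per arm) |
|---|---|---|---|
| 5% | 19.0 | 78.7% | 80.8% (95) |
| 10% | 18.0 | 74.2% | 78.7% (90) |
| 17% | 16.6 | 67.1% | 75.3% (83) |
| 20% | 16.0 | 63.8% | 73.7% (80) |
| 30% | 14.0 | 52.4% | 67.9% (70) |

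**With informative earlier outcomes.** The listed model does include outcomes at all time points, so the table is an upper bound on the attenuation. A simulation checked this with a continuous outcome, one earlier visit, 17% missing at random at the last visit, and regression imputation with residual noise. Share of the effect kept when arm is omitted:

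| Correlation setting | Earlier visit shows none of the effect | Half | All |
|---|---|---|---|
| 0.3 | 0.838 | 0.861 | 0.886 |
| 0.6 | 0.839 | 0.880 | 0.934 |
| 0.8 | 0.832 | 0.906 | 0.979 |

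With arm in the model the share kept was 0.996 to 1.011 throughout, which is full recovery within simulation error. Without it, about 2% to 17% of the effect is lost. The correlations and the timing of the effect are assumptions.

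**The case against.** The strongest reply is that the sentence is inclusive. It does not say that nothing else enters the models, and allocation is known for everyone, so arm can count among the non-missing values. The section also expects the imputed analysis to be close to one based on the observed-data likelihood and commits to analysis by randomised group, which suggests an unlisted term rather than a decision to omit arm. This is a journal article, and a full list of model terms commonly sits in an analysis plan. All of that stands against reading the sentence as an exclusion. It does not remove the point: a predictor list is stated, its plainer reading is outcomes plus demographics, and that reading gives a worse answer than a model with arm.

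A reader might infer more than the article supports:
- *That the effect will certainly shrink.* This requires arm really to be omitted and data to be missing, and observed interim outcomes reduce it. Hospital use is also taken from clinic records, so a missed visit need not mean a missing primary outcome. Relapse number and duration are to be expressed per person-year, so partly followed patients can contribute their observed time.
- *That baseline severity is left out.* Outcomes are assessed at baseline as well as at 3, 6, 9 and 12 months, and they include the mania, depression and adherence measures. The listed outcomes at all time points already cover these scores.
- *That the imputation method alone takes power below 80%.* Loss itself does part of this: 83 observed per arm gives 75.3% with no imputation.
- *That the standard errors would be wrong.* No calculation here shows it.
- *That 17% is the expected loss.* The extra patients also serve the secondary objectives, so 17% is only a ceiling on the allowance.

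**Conclusion.** The point holds conditionally. The article lists the contents of its imputation models without randomised arm, and that list, applied as written, attenuates the between-arm difference. At an assumed 17% missing, equal in both arms, the worst case is 16.6 points instead of 20, with about 67% power before imputation variance. In that case, imputing without arm does worse than analysing the observed patients. Where earlier visits carry the effect, the loss may be as little as about 2% of it; where clinic records or person-time rates supply the primary outcome, it is smaller still. If the investigators already meant to include arm, the amendment only confirms it.

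**What to change.** Amend the sentence in Missing data, for example: *Every imputation model will contain randomised arm (as a covariate, or by imputing within each arm), together with the observed outcomes at baseline and every follow-up visit and the baseline demographics.* Either way of including arm will do. The baseline clinical scores need no separate mention, since they are among the outcomes. Entry route (discharged or referred as an outpatient) may be added because it is known for every patient.

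The cost is one sentence and negligible extra analysis work. Arm can enter as a masked code, so the stated blinding of the statistical analysis is unaffected. The change should be made before any comparison of the arms is seen.

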## Discussion

The final goal of the global mental health policy is to improve the quality of life of patients with mental illness. Pharmacists can contribute to this goal as members of healthcare teams performing pharmaceutical care, and therefore help optimize the mental health services and clinical management processes, through health promotion, and risk reduction of mental illness’ negative effects.

In Colombia, to our knowledge this is the first controlled trial designed to assess the effect of the Dader Method for pharmaceutical care on achievement of therapeutic goals in patients with BD-I (EMDADER-TAB). The primary goal of EMDADER-TAB is reducing the number of hospitalizations, number of emergency service consultations, and the number of unscheduled outpatient visits. The literature has established the impact of the pharmacist in the achievement of therapeutic goals in different diseases and conditions such as cardiovascular disease [33], asthma [34], depression [35], diabetes [36,37], and kidney transplants [38]; however, to our knowledge, there is a lack of randomized controlled trials designed to assess the effect of pharmacist intervention in patients with BD-I [12,39].

Through dispensing, pharmacotherapy follow-up, pharmacovigilance, and health education (pharmaceutical care components), the pharmacist contributes to achieve the best possible outcomes with drug therapy in a particular patient. Pharmacotherapy follow-up is done by identifying, preventing, and solving drug-related problems to improve the expected health outcomes [40]. This study will generate information about the effectiveness of the Dader Method for pharmaceutical care on the achievement of therapeutic goals in patients with BD-I, and will demonstrate the pharmacist’s role in the improvement of medication adherence, therapeutic outcomes, and the solution of drug-related problems in this group of patients. In addition, the study could generate some relevant contributions, both theoretical and practical, in the field of health-related services, as well as program formulations for pharmaceutical care in patients with BD-I. Thus, it will show that pharmacists, in association with the patients, their families, and the health teams, could contribute to achieve the therapeutic goals of BD-I.

The results could be subject to potential biases because: (1) the patients in this study will not be blinded to treatment assignment, and the same pharmacist, who is responsible for collecting trial data, will observe both the control and the intervention group; and (2) control group patients will receive phone calls from the pharmacist, who will encourage their attendance of appointments. These patients will also receive written material and verbal information about BD, MH, and counseling about the importance of adherence to pharmacological and non-pharmacological interventions to achieve therapeutic goals, as requested by the Human Research Ethical Committee in its approval of this research project. The effect of educational written material and the extra attention received by the patients in the usual care group might produce positive outcomes and reduce the magnitude of the differences with the intervention group.

## Trial status

This study is currently recruiting patients.

## Abbreviations

BD: Bipolar disorder; CGI-BP-M: The clinical global impression for bipolar modified; DSM-IV: Diagnostic and statistical manual of mental disorders, fourth edition; DRP: Drug-related problems; HIV: Human immunodeficiency virus; HRSD: Hamilton rating scale for depression; MH: Mental health; NOM: Negative outcomes associated with medication; QF: Quality of life; SJDC: San Juan de Dios Clinic - La Ceja, Antioquia, Colombia; T4: Total T4 or total thyroxine levels; TSH: Thyroid stimulating hormone; YMRS: Young mania rating scale.
